#### Questionnaires {25a, 26}

Participants will complete a series of measures delivered through REDCap, a secure data storage platform maintained by the Centre for Healthcare Innovation in Winnipeg, Manitoba. Questionnaires will be delivered to assess both eligibility and primary and secondary outcomes across both parent and child mental health.

##### Eligibility screener (Main Participants Only)

All primary participants will complete an online eligibility screener to determine if they meet the required inclusion criteria. The eligibility screener consists of several standardized measures to assess depression, anxiety, parenting stress and anger. The Generalized Anxiety Disorder questionnaire (GAD-7; Spitzer et al. [35]) and the Patient Health Questionnaire (PHQ-9 [16]) will be used to examine parental anxiety and depression respectively. These questionnaires ask parents to reflect upon mental health concerns in the past two weeks. Both the GAD-7 (α = 0.92) and the PHQ-9 (α = 0.88) evidence robust internal reliability [16, 35]). The Parenting Stress Index Short Form (PSI-SF) is a 36-item questionnaire that will be used to assess parenting stress. The PSI asks parents to report on a variety of factors including parental distress, parent–child dysfunctional interactions, and difficult child behaviour (e.g., I feel trapped by my responsibilities as a parent; α = 0.87; Abidin et al. [1], Barroso et al. [5]). The Patient Reported Outcomes Measurement Information Symptom [PROMIS] Anger scale will be used to evaluate parenting anger. This ten-item scale asks parents to reflect on experiences of anger in the past seven days (e.g., I was irritated more than people know; α. = 88; Kaman et al. [14]).

##### Pre-intervention, post-intervention and follow-up questionnaires

All eligible participants (i.e., main participants and co-parents) will be asked to complete additional questionnaires that assess other factors known to influence parental mental health such as sleep and self-compassion (i.e. Patient Reported Outcomes Measurement Information Symptom [PROMIS] Sleep Scale [40], The Self-Compassion Short Form Questionnaire [4, 28]). Aspects of the parent–child relationship, child development and family dynamic will also be assessed using a variety of questionnaires (i.e., The Parenting Scale, Irvine et al. [12], Child Behavioral Checklist [3]). Additionally the authors generated an emergency service utilization questionnaire (see Roos et al. [29]) and an adapted version of the National Survey for Children’s Mental Health [8] to assess various sociodemographic, service utilization and health factors related to child and family development. All questionnaires will be completed via REDCap. See Table 1 for a full list of study measures and subsequent timepoints.

**Table 1 Tab1:** Schedule for questionnaire administration: main participant

LightBEAM Proposed Metrics					
Questionnaire	Eligibility	Pre-Intervention	Re-Baselining	Post-Intervention	Follow-Up
Pre-Screener	X				
Patient Health Questionnaire	X	X	X	X	X
Sociodemographic		X			
Generalized Anxiety Disorders	X	X	X	X	X
Self-Compassion		X	X	X	X
PROMIS Anger	X	X	X	X	X
PROMIS Sleep		X	X	X	X
Parenting Stress Index	X	X	X	X	X
Social Support Effectiveness		X	X	X	X
CBCL		X	X	X	X
Parenting Scale		X	X	X	X
App Usage				X	
Service Utilization		X	X	X	X
Modified NMH		X	X	X	X

*PROMIS* Patient Reported Outcome Measurement Information Systems, *CBCL* Child Behavioral Check List, *NMH* National Survey for Children’s Mental Health, *App Usage* Author Generated App usage questionnaire

##### Re-baselining questionnaires

All participants who are randomized to the waitlist control condition will complete an additional set of questionnaires prior to gaining access to the online LightBEAM content. Participants in the waitlist control condition will have a one-month period to complete these questionnaires.

#### Online orientation session

All eligible participants who complete the informed consent procedure will be asked to attend a mandatory online orientation session (approximately 60 min) before gaining access to the LightBEAM program. Parent coaches, who are trained research personnel who previously completed a different iteration of BEAM, will lead the online orientation sessions. Coaches will help orient participants to the app, answer questions about the program, and monitor the closed group forum within the app. Participants will book this online orientation through Microsoft BOOKINGS where they will be able to select a time slot that works best for their schedule. Participants randomized to the LightBEAM program will attend this orientation session shortly after completing pre-program questionnaires. Participants randomized to the waitlist control condition will attend this orientation session after completing the re-baselining questionnaires.

#### Intervention {15a}

The LightBEAM program is a ‘light touch’ extension of the previous BEAM program, meaning it maintains the core principles and theoretical underpinnings used to create BEAM without the direct clinical involvement (Building Emotional Awareness and Mental Health; see Joyce et al. [13], Simpson et al. [33], Xie et al. [38], Xie et al. [39]). The BEAM program is an app-based program developed to support parent mental health, parenting, and healthy child and family development through supporting parental child bonding, and emotion-focused parenting. The BEAM program has traditionally consisted of weekly activities, online group forums, online group-therapy, symptom tracking questionnaires and expert led videos which draw from transdiagnostic emotion-focused mental health and third wave Cognitive Behavioral Therapy principles. To increase the number of families who can access and benefit from the BEAM program, the content has been translated onto a self-guided app-based platform, LightBEAM. The LightBEAM app is being developed by MindSea, a Canadian based digital health solutions company. The LightBEAM app will employ the same expert lead videos, exercises, tip sheets, a group forum and weekly symptom tracking as BEAM (see Joyce et al. [13], Simpson et al. [33]), however LightBEAM will not involve direct clinician contact (i.e. the group therapy and peer coach model will be removed). By removing direct clinician involvement, we effectively increase the scalability of the original BEAM program, allowing a greater number of Canadian families to benefit and access this innovative mental health support.

Following the same structure as BEAM, the LightBEAM program will consist of 12 weeks of parenting and mental health video content (See Table 2). Participants will be instructed to move through the videos and practice exercises at a self-guided pace. The LightBEAM program will consist of four different components; weekly parenting and mental health videos, weekly symptom tracking, a group forum, and exercises designed to reinforce skills learned through the video content.

**Table 2 Tab2:** Schedule for questionnaire administration: co-parent

Questionnaire	Pre-Intervention	Re-Baselining	Post Intervention	Follow-Up
Pre-Screener				
Patient Health Questionnaire	X	X	X	X
Sociodemographic	X			
Generalized Anxiety Disorders	X	X	X	X
Self-Compassion	X	X	X	X
PROMIS Anger	X	X	X	X
PROMIS Sleep	X	X	X	X
Parenting Stress Index		X	X	X
Social Support Effectiveness	X	X	X	X
CBCL				
Parenting Scale	X	X	X	X
App Usage			X	
Service Utilization	X	X	X	X
Modified NMH	X	X	X	X

*PROMIS* Patient Reported Outcome Measurement Information Systems, *CBCL* Child Behavioral Check List, *NMH* National Survey for Children’s Mental Health, *App Usage* Author Generated App usage questionnaire

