### Participant identification, recruitment, and consent {20, 32a}

Participants will be recruited from across Canada using a variety of online social media posts (e.g. Instagram, Facebook), radio ads, and through local organizations (e.g., daycares, community centers etc.). Once recruited, participant informed consent will be obtained via REDCap on two separate occasions; prior to completing the eligibility screener and before becoming enrolled in the program (i.e. before completing pre-questionnaires). Participant Canadian residency will be verified through checking their IP addresses. Should we not be able to verify their residency through IP, we will require participants to upload a photo of their Canadian identification (e.g., driver’s license, passport) alongside a photo of themselves. This verification process is designed to ensure only Canadian residents are accessing the LightBEAM program. The study team has successfully used this form of identity verification across other iterations of BEAM.

During the main consent process, all eligible participants will be asked if they would like to invite a co-parent to complete the LightBEAM program alongside them. Here, we define co-parent as the child’s other parent, stepparent, or other primary caregivers (e.g., child’s grandparents, uncle, auntie, etc.). If the main parent wishes to invite a co-parent to the program, they will be asked to enter their co-parent's email address. The co-parent will then complete a main consent form. Once co-parents have consented, they will go through the same identity verification, randomization, and assessment procedures outlined below.

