### Participant timeline {18}

The LightBEAM program will use a rolling recruitment model whereby eligible participants will be randomized and gain access to the program on the first Monday of each month (e.g., all eligible participants who complete the screener questionnaire during the month of September will be randomized and gain access to the program on the first Monday in October). This rolling recruitment model will continue until the target sample size is reached. While participant timeline in the program will vary within this model, all participants will complete the aforementioned questionnaires in the same order regardless of program start date. Co-parents will engage in the same process described below as the main participant, with the exception that co-parents will not (a) complete the screener questionnaire or (b) complete the Child Behavioral Checklist.

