11	Boundary setting to make space for everything else	Memory making with your kiddo
12	Staying well and moving forward	Recipe for wellness

#### Aim 2

All eligible participants must present with at least one elevated symptom of concern across parental anxiety (GAD-7), depression (PHQ-9), anger (PROMIS) and/or parenting stress (PSI). Based on which metric(s) participants screen in as being elevated, an individualized composite primary score will be created whereby we examine whether there is a statistically significant change in elevated symptoms of concern across assessment time points. To examine the efficacy of the LightBEAM program in improving parental outcomes, a multi-level model with random intercepts will be utilized to assess the effect of treatment over time based on conditions. An intent to treat approach will be followed such that all randomized participants are included in analysis, regardless of completion.

Specifically, we will examine pre-to-post-to follow up program changes in primary and secondary outcomes. Such analysis will allow us to examine the efficacy of the LightBEAM program compared to other community resources. Program engagement metrics (e.g., number of videos watched, see Table 4) will also be included as moderators to probe whether participant changes are due to program engagement. This dosage analysis will be an exploratory analysis.

**Table 4 Tab4:** Aim 1 feasibility and acceptability metrics

	Indicator	Benchmark	Rational
Recruitment Rate	Number of parents recruited per month	Approx. 50 parents	We want at least 50 parents in the forum to ensure maximum engagement
Retention Rate	% of parents with follow up data	> 70% of parents with follow up data	Average retention rate amongst previous MOOI’s is 70%
Forum Use	# of posts and comments made on the forum	> 50% of users engage at least once in the forum (i.e., through posting, responding or interacting with a message)	This is an exploratory outcome. Based on previous work that showed 57% engagement in the BEAM forum
Videos watched	% of videos watched at least 50% of the way through	Participation in > 50% of the LightBEAM Content	Utilizing same benchmark (e.g., 50%) used in previous BEAM pilot studies [13]
Symptom tracking	# of weekly surveys completed	Participation in > 50% of symptom tracking exercises	Based on benchmark used in previous BEAM pilot studies

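### Table 2 gives co-parents no pre-intervention Parenting Stress Index, contradicting the text; if it is followed, their change from baseline cannot be estimated in either arm

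*Protocol article*

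**What the plan says.** Table 2 of the protocol article carries the caption "Schedule for questionnaire administration: co-parent". Its "Parenting Stress Index" row has an empty Pre-Intervention cell followed by marks at re-baselining, post-intervention and follow-up. The table has no eligibility column. Table 1 ("Schedule for questionnaire administration: main participant") marks the same instrument at all five of its time points, including eligibility and pre-intervention.

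The section on participant identification, recruitment and consent says of co-parents: "Once co-parents have consented, they will go through the same identity verification, randomization, and assessment procedures outlined below". The Participant timeline section says they follow the main participant's process "with the exception that co-parents will not (a) complete the screener questionnaire or (b) complete the Child Behavioral Checklist". The eligibility screener, which contains the PSI, is restricted by its own heading to main participants.

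For the analysis, Aim 2 states: "Specifically, we will examine pre-to-post-to follow up program changes in primary and secondary outcomes". All randomised participants are to be included by intention to treat.

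**The concern.** The text names two ways in which co-parent assessment differs from main-participant assessment. A missing baseline PSI is not one of them, yet the table shows it missing. Both cannot be right.

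The conflict matters because it decides what data are collected. Parenting stress is one of the four symptom domains the trial measures, and distress and parenting quality are listed among the primary parent outcomes. Co-parents are randomised, and the stated interest is in change from before the program. A baseline that was never scheduled cannot be collected afterwards, and with monthly intakes every cohort enrolled under the wrong schedule loses it for good.

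**Working it through.** The plan gives no figure to reproduce on this point. The check is a cell-by-cell reading of the two schedules, combined with the text on who completes what and when.

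**Step 1: is the blank a real cell?** Ten instruments in Table 2 are scheduled repeatedly for co-parents. Nine are marked at all four time points: the depression, anxiety, self-compassion, anger, sleep, social support, Parenting Scale, service utilization and modified national survey measures. PSI is the only one without a pre-intervention mark. Its row keeps an empty first cell and then three marks, in line with the header and its neighbours, so a text-extraction fault is unlikely.

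**Step 2: does another assessment fill the gap?** The only other early source of PSI is the screener, which co-parents do not take. Re-baselining is completed by the waitlist arm alone. The Trial design section places it alongside the LightBEAM arm's post-questionnaires, after the 12-week program, within a one-month window. It is therefore not a randomisation baseline.

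**Step 3: PSI measurements by group, if the tables are followed.**

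| Group | Eligibility | Pre-intervention | Re-baselining | Post | Follow-up | Before program access |
|---|---|---|---|---|---|---|
| Main participant, LightBEAM | yes | yes | not applicable | yes | yes | 2 |
| Main participant, waitlist | yes | yes | yes | yes | yes | 3 |
| Co-parent, LightBEAM | no | blank | not applicable | yes | yes | 0 |
| Co-parent, waitlist | no | blank | yes | yes | yes | 1 |

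**Step 4: what can be estimated for co-parents?**

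- Change from baseline, PSI at time t minus PSI at pre-intervention: the second term is absent in both arms, so this cannot be estimated.
- Difference between arms at about 12 weeks, mean LightBEAM post-intervention PSI minus mean waitlist re-baselining PSI: both terms are scheduled, so this can be estimated, but without baseline adjustment.
- Waitlist change from re-baselining to post-intervention: it can be computed, but has no concurrent control.

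**Step 5: does maximum likelihood repair it?** No co-parent would have an observed baseline PSI, so the model has no co-parent information on that value. It could only borrow from main participants, who had to show elevated distress on at least one measure. Co-parents did not have to, so the two groups' baselines need not be alike.

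**The case against.** The strongest reply is that the blank is probably a slip in the table. The text points to co-parents having the full assessment, and nothing in the article shows how REDCap was built. If REDCap follows the text, no data are lost and only the published table is wrong. That stands, and it is why the finding is conditional on Table 2 being followed. A reader might infer that every co-parent already lacks a baseline PSI; the article does not show this.

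Three other strong readings are also unsupported.

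- A reader might infer that no co-parent in either arm has a PSI before using LightBEAM. That is true only of the LightBEAM arm, because waitlist co-parents complete one at re-baselining, before access.
- A reader might infer that the effect on co-parent parenting stress is lost altogether. The comparison of randomised arms at about 12 weeks remains, and randomisation protects it from systematic baseline imbalance. What goes is the change score and the precision that a baseline adds.
- A reader might infer that the primary analysis is damaged. The individualised composite depends on which measures a participant was elevated on at screening. Co-parents are not screened, so as written it is not defined for them with or without a baseline PSI.

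It is also tempting to size the loss by the usual factor 1/(1 − ρ²). With an assumed baseline-outcome correlation of 0.5 to 0.7, this gives 1/(1 − 0.25) = 1.33 to 1/(1 − 0.49) = 1.96. That factor describes a co-parent-only comparison of one post measurement, with and without covariate adjustment. The plan specifies a random-intercept multilevel model over repeated assessments and no separate co-parent PSI analysis, so these figures are not the trial's loss.

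**Conclusion.** The contradiction between Table 2 and the text on co-parent assessment is real and should be resolved. If the table governs, co-parent PSI change from the pre-intervention baseline cannot be estimated in either arm, and the comparison of arms at about 12 weeks must be made unadjusted and with lower precision. The effect is confined to one instrument in an optional, invited group. The article plans for 200–500 caregivers but does not say how many co-parents it expects, so the loss cannot be put as a share of the trial. The conclusion rests on two assumptions: that the empty cell is in the published table, and that data capture follows that table.

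**What to change.** Bring Table 2 into line with the Participant timeline section by marking PSI at Pre-Intervention for co-parents. Check that the REDCap schedule delivers the form at that point, and correct it before further co-parents enrol if it does not. Report by arm how many co-parents were enrolled without a baseline PSI.

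If the omission was intended, list it with the other co-parent exceptions and exclude co-parent PSI from the change analysis, leaving only the unadjusted comparison of arms at about 12 weeks.

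The cost is one 36-item questionnaire added to an online assessment that co-parents already complete.

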#### Psychoeducational video content

LightBEAM program consist of a combination of mental health and parenting content developed by [name] and [name]. Emotion focus parenting strategies, parent management training and theoretical attachment orientations were utilized by [name] to develop the parenting content. [name] and [name] integrated a combination of third wave cognitive behavioral and transdiagnostic emotion focused mental health principles to develop the mental health content.

##### Weekly symptom tracking

Participants will complete two author-generated quantitative weekly symptom tracking exercises to promote emotional awareness [30]. These exercises ask participants to reflect upon how they have felt in the past week across various wellness domains (i.e., individually, interpersonally, socially) and how they have felt in relation to parenting outcomes (i.e., frustration, confidence, relationship quality). Within the app, participant scores on weekly questionnaires will populate a graph that is visible to both participants and researchers (See Simpson et al. [33]).

##### Weekly exercises

Within the app, participants will be prompted to complete weekly exercises designed to reinforce key skills discussed in the weekly psychoeducational video content. Exercises will be completed digitally within the app and include a series of true and false or multiple-choice questions that reflect key concepts learned from that week's content.

##### Group forum

Participants will gain access to a confidential group forum embedded into the LightBEAM app. This forum will be a place for participants to reflect upon the intervention content, engage in dialogue with other participants, ask questions, and offer support. The forum will be monitored daily by parent coaches, trained research personnel who have previously completed BEAM. The coaches will monitor the forum for inappropriate posts and content (e.g., content related to self-harm or suicidality, posts with identifying information) and will also help stimulate group conversation. Furthermore, this forum will offer a place for subsequent qualitative data analysis to further examine feasibility and efficacy of the program.

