### Trial design {12}

Using a two-arm clinical design, participants will be randomized in a 1:1 allocation to be placed in either the 12-week LightBEAM program or the waitlist control. After the 12-week LightBEAM program has been completed by the intervention condition, participants in the waitlist control group will have one month to complete the “re-baselining questionnaires and online orientation prior to gaining access to the LightBEAM intervention. Participants in the intervention condition will complete post-questionnaires at the same time that the waitlist control completes re-baselining questionnaires. Longitudinal self-report questionnaires will be administered digitally at three timepoints: pre-intervention, post-intervention, and at six months follow-up.

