### Criteria for discontinuing or modifying allocated interventions {15b}

Participants will be asked to discontinue treatment if they break the terms of use associated with the LightBEAM app which includes disclosing personal information on the group forum, engaging in inappropriate forum posts, and not respecting the privacy of other participants either on the forum or during the online orientation session. If a participant is asked to discontinue treatment, or if a participant asks to withdraw, we will email the participant and ask if we can use their partial data. If yes, data will be stored in accordance with REB study guidelines. If a participant does not consent, all partial data with the exception of the initial consent form will be destroyed.

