## Methods: data collection, management and analysis

### Data collection methods and management {25a}

All data storage and collection will occur in accordance with the University of Manitoba research ethics boards standards. Participants will be informed during the consent process that they are free to withdraw at any time. Additionally, the study coordinators and principal investigators may remove a participant from the LightBEAM trial if they violate the forum’s terms of use.

Questionnaire data will be collected on REDCap. Data captured within the LightBEAM app (i.e., participant weekly questionnaire response and forum posts) will be stored on a Firebase Server and data storage located in Montreal, Canada in the Google cloud.

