### Definition of analysis population related to protocol non-adherence and methods to handle missing data {27c}

The LightBEAM program will employ an intent-to-treat analysis using maximum likelihood estimation, whereby all participants, regardless of study completion and adherence, will be included in analysis based on their initial randomization. To account for treatment adherence, de-identified analyses will be conducted using only data from participants who completed the LightBEAM intervention.

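### Read literally, the rule on inappropriate forum posts lets a disclosure of suicidal thoughts count as a ground for asking a participant to stop the programme

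*Protocol article*

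**What the plan says.** Three places in the protocol article bear on the rule.

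- **Group forum.** Parent coaches check the forum every day: "The coaches will monitor the forum for inappropriate posts and content (e.g., content related to self-harm or suicidality". The second example in the same bracket is posts that contain identifying information. The section attaches no sanction.
- **Criteria for discontinuing or modifying allocated interventions {15b}.** This section sets the main rule: "Participants will be asked to discontinue treatment if they break the terms of use associated with the LightBEAM app". The breaches named are "disclosing personal information on the group forum, engaging in inappropriate forum posts, and not respecting the privacy of other participants".
- **Data collection methods and management {25a}.** A second removal rule, tied to the forum's terms of use, says that "the study coordinators and principal investigators may remove a participant from the LightBEAM trial if they violate" those terms. This one is discretionary.

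Safety text appears elsewhere. Confidentiality {33} allows confidentiality to be broken when imminent danger to self or others is disclosed. Research ethics approval {30} sends adverse events to the ethics board. Ancillary and post-trial care {34} gives everyone a list of crisis resources after the screener. None of these sections mentions discontinuation.

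**The concern.** The same adjective does two jobs. In the forum section it labels content that signals risk to the participant. In {15b} it labels behaviour for which a participant is asked to stop. Put together, the printed rule treats a cry for help as a breach of conduct.

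The population makes this more than a drafting point. Main participants qualify by reporting at least mild depression, anxiety, anger or parenting stress (Eligibility criteria {14a}). The programme has no direct clinician contact (Intervention {15a}), and the people reading the posts are parent coaches rather than clinicians in a treating role. The coaches and coordinators need to know whether a post about suicidal thoughts calls for a safety response or a disciplinary one. At stake is the safety of a participant who might be asked to give up support just when they have disclosed a need for it.

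**Working it through.** No arithmetic applies: the point contains no figure, and the document gives no rate of such posts. The check is a comparison of the texts.

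1. **What does the article say is inappropriate?** Only the Group forum section illustrates the term. It gives two examples: self-harm or suicidality content, and posts with identifying information.
2. **What leads to a request to stop?** Section {15b} names three breaches: disclosing personal information, inappropriate forum posts, and not respecting others' privacy. The request is worded as something that will happen.
3. **Do the two lists line up?** Only in part. Identifying information, the second forum example, resembles the first breach in {15b}, which is listed on its own. That leaves self-harm or suicidality as the only illustrated content for the separate breach of inappropriate posts. The separate listing also shows that {15b} may divide the category differently from the forum section, so the match is plausible but not proved.
4. **Is there an exception anywhere?**
   - Group forum: none.
   - {15b}: none.
   - {25a}: staff may choose not to remove someone, but no exception is named.
   - Strategies to improve adherence {15c, 25b}: questionnaires are encouraged whatever the level of participation, but the section does not address people asked to stop.
   - {30}, {33} and {34}: each can operate alongside a request to stop, and none prevents one.

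Result: read literally, the printed text covers a safety disclosure, and nothing printed takes it out again.

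**The case against.** The strongest reply is that the operative test in {15b} is breach of the app's terms of use. Those terms are not shown, and a journal article commonly leaves such detail to a fuller document. The forum sentence describes monitoring and carries no penalty. The breaches in {15b} read naturally as misconduct. Daily monitoring, the confidentiality exception for imminent danger, adverse-event reporting and discretionary removal all suggest that escalation is what the investigators intend.

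Most of this stands. It lowers the confidence and makes the point minor. It does not remove it, because the complaint is not that a detail is missing: the article prints an example and a ground which, taken together, reach too far. Narrower terms of use would settle practice, but the published wording would still need correcting.

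A reader might infer two stronger claims, and the document supports neither.

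- **That caregivers who disclose suicidal thoughts will be expelled.** The link rests on one shared word, removal under {25a} is discretionary, and the terms of use are not shown.
- **That the forum wording biases the trial by destroying data, mainly in the LightBEAM arm.** Section {15b} does say "If a participant does not consent, all partial data with the exception of the initial consent form will be destroyed". But that rule also applies to anyone who asks to withdraw, in either arm, and depends on the participant's own refusal. It does not arise from the forum wording. A loss by this route would need a disclosure, a decision to treat it as a breach, a request to stop and a refusal of data use. The document gives a frequency for none of these steps.

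**Conclusion.** The point holds as a minor safety clarification, with low to medium confidence. The printed rule is drawn too broadly. It is not a contradiction between sections, and escalation is probably what is meant.

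Its size cannot be expressed as a number, because the document gives no basis for estimating how often such posts would occur. No material effect on the treatment estimate is claimed.

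The conclusion assumes that the word carries the same meaning in the forum section and in {15b}, and that the unseen terms of use contain no exception. If either assumption fails, practice is already safe and only the published wording needs attention.

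**What to change.** - **Group forum:** take self-harm or suicidality content out of the examples of inappropriate posts. List it separately as a safety flag that coaches escalate to the study team, handled together with {30} and {33}.
- **{15b}, {25a} and the app's terms of use:** limit discontinuation and removal to conduct breaches, namely identifying information, abuse and violations of others' privacy. State that a safety disclosure alone is not a ground.
- **Follow-up:** state that the person stays on the scheduled questionnaires, in line with {15c, 25b}.

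The clinical response to a flagged post is for the investigators to settle.

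The cost is rewording these sections and the terms of use, plus an amendment through the ethics board under Protocol amendments {31}. Coaches would sort flagged posts into two categories instead of one. No additional assessments are needed.
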